## Abstract

The current state of knowledge related to diet in Hashimoto thyroiditis (HT) is far from satisfactory, as many HT subjects experience several disorders and report reduced quality of life. There are three aims of the study: (1) to develop a qualitative dietary protocol (QDP; ‘Diet4Hashi’) as a simple, graphic–text tool dedicated to TH subjects, (2) to evaluate the use of the QDP in dietetic counseling compared to conventional dietetic counseling (CDC) in HT women, and (3) to assess the impact of both the QDP and the CDC on the diet quality, quality of life, adiposity, and metabolic parameters of HT women. The QDP is based on subject self-monitoring supported with a graphic–text tool to help them in food selection and adequate food frequency consumption, while the CDC on oral explanation and printed sample menus were provided by a dietician. The QDP contains two lists: (A) foods recommended for consumption and (B) foods with limited consumption, along with indicated consumption frequency per day/week/month. Both approaches include the same dietary recommendations for HT extracted from the literature but differ in subject–dietician cooperation. To summarize the evidence regarding dietary recommendations in HT, the PubMed, Embase, and Cochrane Library databases (to March 2019) and the bibliographies of key articles were searched. The study is designed as a dietary intervention lasting six months in two parallel groups: experimental and control. In the experimental group, the QDP will be applied, while in the control group, the CDC will be applied. In total, the study will include a baseline of 100 women with diagnosed HT. The subjects will be randomly allocated into the experimental/control groups (50/50). Data related to diet quality and other lifestyle factors, nutrition knowledge, quality of life, thyroid function, body composition, blood pressure, serum fasting glucose, and lipid profile at baseline and after a six-month follow-up will be collected. This study was conducted to develop a dietary protocol (Diet4Hashi) that is easy to follow for HT subjects, and it will contribute to providing valuable data that are useful to dieticians and physicians. It is anticipated that this graphic–text qualitative dietary protocol, by improving food selection and diet quality, may reduce adiposity and improve metabolic parameters and the quality of life of HT women.

## 1. Introduction

Chronic lymphocytic thyroiditis (Hashimoto thyroiditis, Hashimoto, HT) is the most frequent autoimmune disorder and the cause of hypothyroidism in iodine-sufficient countries [1,2,3]. The prevalence of primary hypothyroidism affects 1%–3% of the population, while subclinical hypothyroidism is more common (estimated at 4%–10%). Abnormal functioning of the thyroid gland is diagnosed in 22% of the population [4,5,6]. In Poland, almost 1.5 million cases of thyroid gland diseases were diagnosed in 2004–2009 in surveys on women’s health [7,8]. Women had thyroid gland disease almost nine times more often than men. Within five years, the number of women declaring thyroid disease increased by 1.4 percentage points in 2009 compared to 2004. Data on HT prevalence in Poland is missing. Findings from the National Health and Nutrition Examination Survey (NHANES) III showed that the prevalence of HT was 4.8 per 1000 USA residents [9]. 

Thyroid hormones control growth, metabolism, and body development and take part in the production of structural proteins, enzymes, and other hormones. The majority of subjects with thyroid disease experience problems in maintaining normal body weight and have a higher body mass index and waist circumference than healthy subjects [10]. Herwig et al. [11] showed that the total metabolic rate can be lowered by up to 50% in serious cases of hypothyroidism. Lowering the total metabolic rate supports body weight gain and predisposes patients to obesity, even when a patient’s physical activity and dietary energy load are the same as before hypothyroidism diagnosis. Incorrect energy conversion worsens the functioning of most body tissues and disturbs metabolism, including glucose metabolism [12]. Findings from the Polish study (2001–2010) showed that HT co-occurred with diagnosed diabetes in over 27% of HT subjects and fasting blood glucose level or impaired glucose tolerance in about 17% of HT subjects [13]. Furthermore, even after normalizing thyroid function via hormonal replacement, many HT individuals persist with numerous symptoms, such as chronic fatigue and irritability, dry skin, hair loss, nervousness, and impaired quality of life [14].

Medical management with thyroid hormone replacement is the fundamental treatment in HT [15,16]. Nutrition can support the treatment and the impact of diet on thyroid function cannot be denied, as dietary micronutrients play a role in thyroid hormones synthesis. To date, there is limited information from well-evidenced studies, and none of the scientific societies have developed comprehensive dietary recommendations on HT [17,18,19,20,21]. The recommendations of the American Thyroid Association [19] and the American Dietetic Association [20] refer exclusively to thyroid cancer and the intake of iodine and salt. A recent review by Liontris [18] described the role of iodine, selenium, vitamin D, and gluten in the dietary management of HT patients. A gluten-free diet was considered potentially beneficial for HT patients independently of a comorbid diagnosis of celiac disease [17,18]. However, it was speculated that in subjects ‘on a diet’, their quality of life may be negatively impacted due to the restrictive nature of a gluten-free diet [17,18,21]. Abbott et al. [22] reported an improvement in health-related quality of life and clinical symptom burden in TH women after implementation of a phased elimination diet known as the Autoimmune Protocol supported by a multi-disciplinary team with a 10-week online diet and lifestyle coaching. Despite this, no significant changes in thyroid function or thyroid antibodies were found. Thus, many dieticians have difficulties in summarizing study findings and developing practical dietary recommendations. On the other hand, there has been growing interest in dietary counseling, due to an increasing number of HT subjects. Patients who are weakly supported by dieticians or other health professionals seek advice from other sources, e.g., mass media and the Internet, including those from less credible sources and/or giving contradicting information. 

### 1.1. Research Objective and Hypothesis

The current state of knowledge related to diet in HT is far from satisfactory, while many HT subjects experience many disorders and report reduced quality of life [13,14,18,23]. There is a strong need to summarize the evidence and develop dietary recommendations that are simple for HT subjects to understand and implement daily over a long-term period, and are useful for dieticians and other health professionals. The conventional approach to dietetic counseling is a structured process aimed at supporting individual patients to modify their dietary behaviors to improve health outcomes [24]. Conventional dietetic counseling is based on the development of individual recommendations and formulating detailed guidelines, which may prove difficult for patients to follow over the long term due to growing fatigue, lowering of motivation, the time required, and difficulties maintaining subject compliance to the diet [25]. Mitchell et al. [24] reported that dietetic counseling appears to be effective, e.g., in improving diet quality, diabetes outcomes, and weight loss outcomes, while limited evidence was found for the effectiveness of direct dietetic counseling alone in achieving outcomes relating to plasma lipid levels and blood pressure. The authors suggested that future research might explore novel nutrition counseling approaches.

There are three aims of the study: (1) to develop a qualitative dietary protocol (QDP; ‘Diet4Hashi’) as a simple, graphic–text tool dedicated TH subjects, (2) to evaluate the use of the QDP in dietetic counseling compared to conventional dietetic counseling (CDC) in HT women, (3) to assess the impact of both the QDP and the CDC on diet quality, quality of life, adiposity, and metabolic parameters. It is planned to develop a food-only protocol without considering the use of supplements because an adequate, well-balanced diet should be the first step in a dietary approach to improving health.

The research hypotheses are:Dietetic counseling with the use of a qualitative dietary protocol can facilitate patient understanding and long-term adherence to dietary recommendations compared to conventional dietetic counseling.A well-composed diet supported with a simple, qualitative dietary protocol, by improving food selection and diet quality, can improve the quality of life of HT subjects, reduce adiposity, and improve metabolic parameters. Furthermore, a better effect of a qualitative dietary protocol than conventional dietetic counseling is possible.

### 1.2. Study Design

The study is designed as a single-center dietary intervention lasting six months, with a random allocation of HT women into two parallel groups: experimental and control. In the experimental group, the QDP will be applied, while the CDC will be applied in the control group. The QDP is based on subject self-monitoring supported with a graphic–text tool to help them in food selection and adequate food frequency consumption, while the CDC will be supported by an oral explanation and printed sample menus given by dietician. Both approaches include the same dietary recommendations for HT, extracted from the literature, but differ in subject–dietician cooperation. 

The schedule of the enrolment, intervention, and data collection is presented in Table 1. All data will be collected at the same time for both groups, with one exception. The experimental group, supported with a graphic–text tool, will be asked to complete self-monitoring diaries during the six months of the study.

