In the QDP group, dietetic counseling will be supported with a simple tool containing two lists: (A) foods recommended for consumption (seven items) and (B) foods with limited consumption (six items), both with an indicated consumption frequency per day/week/month (Table 3 and Table 4, in Polish: Tables S3–S4). To develop both lists, we summarized data collected from the literature search and extracted recommended frequencies of food consumption, dividing foods on those recommended for more frequent consumption (list A) or less frequent consumption (list B). If the state of knowledge was unclear or findings were contradictory or poorly documented, then guidelines for the general population were adopted [30] to establish consumption frequency per day/week/month. Each food list is developed as a graphic–text self-monitoring diary to help patients in food selection and to exercise self-monitoring of food consumption and facilitate compliance with dietary guidelines. The printed version of the self-monitoring diary will be distributed, and participants will be asked to complete a diary for six months and return it during a visit. Respondents’ adherence to dietary guidelines will be expressed in points; one point per each compliance to each recommendation will be assigned. All points will be summarized to express an adherence score to the QDP an Adherence Score to the QDP (AdhS; ranged 0-13 points). Data from six months will be collected, and the mean AdhS will be calculated. The AdhS will be considered on three levels—low (0–4 points), average (5–9 points), and high (10–13 points)—and interpreted; more points indicates better compliance with dietary guidelines.

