### 2.12. Statistical Analysis

Categorical variables will be presented as a sample percentage (%) and continuous variables will be presented as means with a 95% confidence interval (95%CI) or medians with an interquartile range (IQR) for variables with normal or non-normal distribution, respectively. To assess the impact of dietetic counseling and verify the differences between the experimental and the control group, two-tailed tests will be applied; *p*-values < 0.05 will be considered significant. 

The normality of variable distribution will be verified with a Kolmogorov–Smirnov test before the statistical analysis. For continuous variables, e.g., diet quality scores, AdhS, scores of QoL, nutrition knowledge score, TFTs, markers of adiposity, metabolic parameters, and changes after a six-month follow-up with respect to baseline will be verified with a T-test for dependent samples or a Mann–Whitney test, for variables with normal or non-normal distribution, respectively. For categorical variables, logistic regression modeling will be applied to determine the chance of the occurrence of high diet quality, high AdhS, high QoL, as well as low adiposity and elevated metabolic parameters. The odds ratios (ORs) and 95% confidence intervals (CIs) will be calculated. The significance of ORs will be verified with Wald’s statistics. A crude model and models with an adjustment for confounders will be created. All analyses will be performed with Statistica software (version 13.3 PL; StatSoft Inc., Tulsa, OK, USA; StatSoft, Krakow, Poland).

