The main limitation is that the study will not have a controlled placebo as there is no ‘dietetic placebo’ for dietetic counseling. Therefore, the graphic–text tool will be controlled with conventional dietetic management. Secondly, the study is not double-blinded because (i) the researcher who will be involved in dietetic counseling will be aware of which participants are included in the QDP group and which participants are in the CDC group, and (ii) it is possible that respondents may be aware of what dietetic counseling they are following. The next limitation is the use of non-thyroid-specific food frequency questionnaires (FFQs) to describe diet quality. Both FFQs have been previously used to study the association between diet and health outcomes in the context of non-alcoholic fatty liver disease [89], celiac disease [90], metabolic syndrome [91], breast and lung cancers [92,93], and are accurate tools to describe overall diet quality as well as negative (nHDI) or positive (pHDI) aspects of diet quality. Unfortunately, both FFQs do not contain any detailed specification of food items that are important (more or less recommended for consumption) in the ‘Hashi diet’ (e.g., buckwheat grain or cruciferous vegetables). This limitation will be reduced by a quantitative (in points) assessment of the consumption frequency of those foods, which was recorded in real time via a self-monitoring diary, to assess adherence to the QDP. Further limitations can be attributed to using FFQs. Although there is evidence of many advantages related to data collection with the FFQs, several shortcomings have been reported, e.g., the data relies heavily on memory; therefore, declining cognitive ability may result in errors when reporting on food frequency consumption; the food list cannot cover all the foods consumed by respondents, which may lead to underreporting; and the use of a questionnaire causes some uncertainty due to social desirability bias, especially in females, who may provide more socially acceptable answers [94]. To describe sedentary (screen time) and active behaviors (at leisure time and work), a questionnaire with simple questions will be used. This will allow respondents to be ranked into categories of low and high physical activity levels, but will not allow precise measurement of physical activity. Office measurements of blood pressure will be taken, so ‘white coat’ hypertension phenomena should be taken into account when elevated blood pressure is interpreted [42,43]. Future studies should consider applying other methods to fully describe subjects’ dietary behaviors (e.g., biomarkers and/or repeated food records) and measure physical activity (e.g., accelerometry) instead of self-reported data [94,95] and also implement repeated blood pressure measuring (e.g., 24-hour monitoring) [42,43]. 

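### The adherence score (AdhS) exists only in the QDP arm and has no baseline, so it cannot test the between-arm adherence part of hypothesis 1

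*Protocol article*

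**What the plan says.** All references are to the protocol article.

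- **Hypothesis (section 1.1).** Counseling with the QDP "can facilitate patient understanding and long-term adherence to dietary recommendations compared to conventional dietetic counseling". It has two parts, understanding and adherence, and both are comparative.
- **Content of the arms (section 1.2).** "Both approaches include the same dietary recommendations for HT". Adherence to those recommendations is therefore a meaningful quantity in both arms.
- **Data collection (section 1.2, Table 1).** "All data will be collected at the same time for both groups, with one exception". The exception is the diary: "The experimental group, supported with a graphic–text tool, will be asked to complete self-monitoring diaries during the six months of the study". Table 1 places it between T1 and T2 and between T2 and T3, for the experimental group only.
- **Score (section 2.4, Tables 3 and 4).** One point is given for each recommendation met, over seven List A items (minimum frequencies) and six List B items (maximum frequencies), for a range of 0 to 13. A mean is taken over six months and graded "low (0–4 points), average (5–9 points), and high (10–13 points". The patient makes a mark each time a listed food is eaten.
- **Analysis (section 2.12).** The continuous variables are given as "diet quality scores, AdhS, scores of QoL, nutrition knowledge score, TFTs, markers of adiposity, metabolic parameters", in the sentence that sets out the tests of six-month change from baseline. High AdhS is also named as an outcome for logistic regression.
- **Acknowledged limitation (section 3.3).** "both FFQs do not contain any detailed specification of food items that are important". The remedy offered there is the self-monitoring diary.

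**The concern.** A comparative hypothesis needs the same measurement in both arms. Here the one instrument built to measure adherence to the Hashimoto recommendations is also part of the experimental intervention, and the control arm never receives it. The remedy in section 3.3 for the questionnaire's lack of detail therefore works in one arm only.

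The gap lies in what is collected, which the protocol fixes, and not in how it is analysed. A later analysis plan cannot create CDC diary data or a pre-intervention diary score. If nothing changes, the adherence part of the first-listed hypothesis will rest on a proxy that the article does not designate for that purpose.

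**Working it through.** **1. Reproduce the score range.** AdhS = (List A items with frequency at or above the minimum) + (List B items with frequency at or below the maximum). The maximum is 7 + 6 = 13, which agrees with the stated range of 0 to 13.

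**2. Count the AdhS values available for each analysis** (planned allocation of about 50 per arm, section 2.3).

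| Quantity | QDP | CDC |
|---|---|---|
| AdhS before or at T1 | 0 | 0 |
| AdhS over the six months | up to about 50 | 0 |

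A between-arm difference needs both cells of the second row, and one is empty. A change from baseline needs the first row, and both cells are empty. A logistic model of high AdhS can be fitted within QDP, but it cannot contain the arm as a factor.

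**3. Check the proxy collected in both arms.** KomPAN is taken in both arms at T1, T2 and T3 (Table 1). Setting the 24 scored items of section 2.5 against the 13 diary items:

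- *At least partly matched (10):* vegetables, calcium-rich foods, fruit, whole grains, zinc-rich animal foods (through red meat), fish, sweets, sweetened and energy drinks, fast food, alcohol.
- *No direct match (3):* nuts and seeds, raw cruciferous vegetables, soybean and millet.
- *Direction:* nHDI counts cheese and red meat toward a worse diet. List A names cheese among the calcium-rich foods, and beef, lamb and pork among the zinc-rich foods, as recommended. A patient who follows List A can therefore score worse on nHDI.
- *Recall:* section 2.5 asks about the last 12 months. At T3, six months after baseline, 6/12 = 50% of that window is before the intervention. At T2 (one month) it is 11/12, about 92%. If patients average faithfully over the window, a real change that began at T1 would appear at about half its size at T3.

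**4. Secondary: the score as literally written.** List B items are maxima and only eaten foods are marked, so a food not eaten and a food not recorded look the same.

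- A blank page scores 0 (List A) + 6 (List B) = 6, inside the average band of 5 to 9.
- True score 3, with one of six months recorded: (1×3 + 5×6)/6 = 33/6 = 5.5, which is no longer low.
- True score 12, with three of six months recorded: (3×12 + 3×6)/6 = 54/6 = 9.0, which drops from high to average.

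These figures assume that blank months are scored and that the mean is taken over six monthly scores. The article states neither.

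**5. Secondary: the level boundaries.** The bands are whole numbers, but the graded quantity is a mean. Three months at 9 and three at 10 give (27 + 30)/6 = 9.5, which falls between average and high. This example involves no blank pages.

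**The case against.** **Hypothesis 1 is not wholly untestable.** This is the strongest point on the other side, and it stands. A reader might infer that the trial will have no comparative information on adherence, or that the whole hypothesis fails. The documents do not support that. Understanding can be approached through the nutrition knowledge score, taken in both arms at T1 and T3. KomPAN covers 10 of the 13 diary items at least in part, in both arms, and section 3.3 says that detail is lacking for some foods, not that the instrument is uninformative. What remains is that KomPAN is indirect, with the recall and direction problems shown above.

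**Section 2.12 is loosely worded.** The sentence can be read as listing AdhS simply as a variable, with change from baseline as a further entry. The logistic model of high AdhS is not said to compare arms, and a model of its predictors within QDP would be valid. This is fair. It makes the analysis text unclear rather than certainly wrong, but it does not supply the missing comparison.

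**The blank-diary score is inferred.** A reader might conclude that patients who stop recording will be graded moderately adherent. No passage says that an unfilled diary is scored, and a rule for missing diaries may stand in a fuller document. The point is therefore conditional.

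**The main outcomes are unaffected.** The sample size in section 2.11 rests on overall quality of life and BMI, and neither uses AdhS. That is correct, and it limits the reach of the finding.

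**Conclusion.** The point holds for the adherence part of hypothesis 1. As designed, AdhS provides 0 of about 50 control values and no baseline values, so it cannot supply the between-arm comparison or a change from baseline. This follows directly from sections 1.2 and 2.4 and Table 1 and needs no outside assumption. pHDI and nHDI leave 3 of 13 items without a direct match, draw half of their T3 recall window from before the intervention, and partly run against List A. They are a weak substitute, though not an empty one.

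The blank-page score of 6 out of 13 is secondary and holds only if unfilled periods are scored literally. The gap between levels is minor, but it is in the text itself. The quality-of-life, BMI, diet-quality and metabolic comparisons do not depend on any of this.

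**What to change.** 1. **Use one common instrument.** Give both arms a short 13-item frequency checklist (the List A and List B items, last month) at T3, scored 0 to 13. Make the between-arm difference at T3 the test of the adherence part of hypothesis 1. Giving it only at T3 avoids showing CDC patients the content of the experimental tool during the intervention.
2. **Adjust for baseline.** Use the matching KomPAN items at T1 as the baseline covariate, and report the same items at T3 as a supplement. These are already collected.
3. **Confine AdhS.** State in section 2.12 that AdhS is not analysed as a change from baseline or between arms, and that any AdhS or high-AdhS analysis is descriptive or predictive within QDP.
4. **Separate blank from not eaten.** Add a tick for diary completed or none eaten, and treat unticked periods as missing. Dropping every day without a List A mark would not do: it would delete days that are truly non-adherent and break the weekly and monthly limits, which need whole calendar periods.
5. **Define the levels for a mean score:** below 5, 5 to below 10, and 10 or above.

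The cost is one extra page at one existing visit, a tick column in the diary and a few sentences of text. One limit remains: a last-month checklist at T3 describes adherence at the end of the study, not over all six months. If the checklist is not added, the adherence part of hypothesis 1 should be restated as a description within QDP.
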